## Abstract

**Methods::**

In this prospective, multicenter, randomized, double-blind, double-dummy, placebo-controlled trial, we will assigned 673 eligible patients with AMI after reperfusion into 4 groups: receiving Nao-Xin-Tong capsule (NXT), Bu-Yang-Huan-Wu (BYHW) granule (BYHW), Yang-Yin-Tong-Nao granule (YYTN), or placebo. The course of treatment will be 3 months. The primary outcome is HF incidence within 180 days. Nao-Xin-Tong capsule, BYHW granule, and Yang-Yin-Tong-Nao granule are different traditional Chinese medicines used for tonifying Qi and activating blood (TQAB).

**Results::**

Three months of TQAB combined with Western medicine may reduce the incidence of HF after reperfusion of AMI and improve patients’ quality of life.

**Discussion::**

This study will provide an important basis for the application of traditional Chinese medicine in patients with AMI after reperfusion and provide an evidence-based basis for the prevention and treatment strategy of HF after AMI.

## 2. Methods/design

### 2.1. Design

This is a prospective, multicenter, randomized, double-blind, double-dummy, placebo-controlled trial. It will be conducted at the Beijing Hospital of TCM affiliated to Capital Medical University and member units of the Beijing Office of Cardiovascular Disease Prevention and Treatment from December 2019 to December 2022. We will recruit 673 patients with AMI after reperfusion and assign them to Nao-Xin-Tong (NXT), Bu-Yang-Huan-Wu (BYHW), Yang-Yin-Tong-Nao (YYTN), or control groups. All participants will receive basic drug treatment according to the 2018 Guidelines for the Diagnosis and Treatment of AMI with Integrated Traditional Chinese and Western Medicine.^[15]^ The study drugs will be administered for 90 days. The patients will be followed-up for 180 days. The flowchart of the study design is shown in Figure 1.

**Figure 1. F1:**
[figure not shown]
The flow chart of the study design. BYHW = Bu-Yang-Huan-Wu, HF = heart failure, MACE = major adverse cardiovascular events, NXT = Nao-Xin-Tong, SAQ = the Seattle angina questionnaire, TCM = traditional Chinese medicine, YYTN = Yang-Yin-Tong-Nao.

### 2.2. Ethics approval

The trial was registered on June 18, 2021, in the Chinese Clinical Trial Registry (registration no. ChiCTR2100047435) and was reviewed and approved by the Ethics Committee of Beijing Hospital of TCM, affiliated to Capital Medical University (No. 2020BL02-019-01). This trial will be conducted in accordance with the Declaration of Helsinki, and the protocol will follow the recommendations of SPIRIT 2013^[16]^ (see Additional file 1). All the participants provided written informed consent.

### 2.3. Recruitment

We plan to recruit 673 participants from the outpatient or inpatient wards of the Beijing Hospital of TCM affiliated to Capital Medical University and member units of the Beijing Office of Cardiovascular Disease Prevention and Treatment. The researcher will take the initiative to introduce this trial, and the participants will voluntarily participate in the project. After screening by a clinician according to the inclusion and exclusion criteria, patients will be enrolled.

### 2.4. Inclusion criteria

Patients who fulfilled all of the following inclusion criteria will be included in this study: diagnostic criteria for AMI^[17]^ and atherosclerotic type^[18]^; diagnostic criteria for^[19]^ Qi deficiency and blood stasis syndrome; 2 weeks after successful reperfusion; 18 to 80 years of age, including men and women; and agreed to participate and sign an informed consent form.

### 2.5. Exclusion criteria

Patients with one of the following criteria will be excluded: severe liver or kidney insufficiency (alanine aminotransferase, ALT > 3 times the normal level; serum creatinine > 221 μmol/L); serious consumption state or malignant tumor; pregnancy or lactation; suspected or definite allergy to the test drug; participation in other clinical studies in the past 3 months; use of any preparation containing the same ingredients within 2 weeks; continuous mechanical adjuvant therapy after successful interventional therapy; and inability to actively cooperate with the treatment.

### 2.6. Withdraw criteria and management

Participants will be allowed or required to withdraw from the trial if they: develop a serious disease that is not suitable to continue in the investigator’s opinion; serious adverse events occur; and request to withdraw from the trial.

### 2.7. Randomization and grouping

A stratified random method will be adopted in the experiment with centers as the stratified factor. A total of 673 patients who fulfilled the criteria will be randomized into the NXT, BYHW, YYTN, and placebo groups in a 2:1:1:1 ratio. Randomized numbers will be generated by independent statisticians using SAS9.4 software (Beijing Hospital of TCM Version. Order number: 9C1XJD). Randomized numbers, rank sequences, and groupings will then be stored in opaque envelopes maintained by designers and statisticians throughout the study. All envelopes will be given running serial numbers, and each patient received one. Patients will be allocated to different groups according to the contents of the envelopes. Each participant received treatment assigned according to the randomization list. All clinical personnel and outcome assessors will be blinded to the intervention.

### 2.8. Blinding method

The double-blind and double-dummy methods will be used in this study. The first level of blindness will be the randomly coded group (groups A, B, C, or D) and the second level will be the treatment plan (experimental drug or placebo) for each group. The designer, researchers, and statisticians jointly will conduct the first unblinded and locked data analysis. Statistical analyses will be performed on the 4 sets of data under the supervision of an ethics committee. After the data analysis, a second uncovering will be conducted. The outcome information gatherers and outcome evaluators will be third-party statisticians who will not participate in study design or patient recruitment. The random coding table will be set up by the Clinical Trial Data Management and Statistics Unit, blind-sealed in duplicate, and stored by the designer and statistician in two locations for safekeeping. The entire drug-coding process will be documented by the compiler. That is, a blind record will be retained as one of the files of the clinical study. Blind emergency broken letters shall be kept by the clinical test unit and no one shall open them without permission. When serious adverse events occur during a study or when patients need to be rescued, it is necessary to know the patient’s treatment. Emergency blindness can be overcome by using trial centers. If patients experience severe adverse events, physicians should administer the relevant treatment. Emergency blindness will be determined by the principal investigator in the clinical trial unit. The reason, time, and location of blindness will be recorded in detail. The data remained intact even after blindness.

### 2.9. Intervention method

All patients will undergo basic treatment according to the 2018 Guidelines for the Diagnosis and Treatment of AMI with Integrated Traditional Chinese and Western Medicine. Drugs include antiplatelet agents (aspirin and clopidogrel), statins, beta blockers, nitrates, and angiotensin-converting enzyme inhibitors. Patients in the NXT group will be administered 4 Nao-Xin-Tong capsules and one bag of placebo granules thrice daily. Patients in the BYHW group will be administered one bag of BYHW granules and 4 placebo capsules 3 times daily. Patients in the YYTN group will be administered one bag of Yang-Yin-Tong-Nao granules and 4 placebo capsules 3 times daily. Patients in the placebo group will be administered one bag of placebo granules and 4 placebo capsules 3 times daily. The research drugs will be provided by Buchang Pharmaceuticals Limited Company. Placebo capsules and granules will be packaged in the same size, color, and taste as those of the study drugs. The treatment will last 90 days. The main components of the study drugs are listed in Table 1.

**Table 1 T1:** The main components of the study drugs.

Drug	Chinese name	Latin name
Nao-Xin-Tong capsule	Shenghuangqi	Astragali Radix
	Chishao	Paeoniae Radix Rubra
	Danshen	Salviae Miltiorrhizae Radix et Rhizoma
	Danggui	Angelicae Sinensis Radix
	Chuanxiong	Chuanxiong Rhizoma
	Taoren	Persicae Semen
	Honghua	Carthami Flos
	Zhiruxiang	Olibanum
	Zhimoyao	Myrrha
	Jixueteng	Callerya reticulata (Benth.) Schot
	Niuxi	Achyranthis Bidentatae Radix
	Guizhi	Cinnamomum cassia Presl
	Sangzhi	Morus alba L
	Dilong	Pheretima
	Quanxie	Scorpio
	Shuizhi	Hirudo
Bu-Yang-Huan-Wu granule	Shenghuangqi	Astragali Radix
	Dangguiwei	Angelicae Sinensis Radix
	Chishao	Paeoniae Radix Rubra
	Dilong	Pheretima
	Chuanxiong	Chuanxiong Rhizoma
	Honghua	Carthami Flos
	Taoren	Persicae Semen
Yang-Yin-Tong-Nao granule	Shengdi	Rehmanniae Radix
	Shihu	Dendrobii Caulis
	Shenghuangqi	Astragali Radix
	Gegen	Puerariae Lobatae Radix
	Shuizhi	Hirudo
	Chuanxiong	Chuanxiong Rhizoma

### 2.10. Outcome evaluation

#### 2.10.1. Primary outcomes.

The primary outcome of this study is HF incidence. These data will be recorded over 180 days.

#### 2.10.2. Secondary outcomes.

Recurrence rates of other major adverse cardiovascular events, such as AMI, all-cause mortality, readmission rate due to cardiovascular events, non-fatal stroke, non-fatal AMI, and cardiovascular death, will be recorded by outpatient and telephone follow-up within 180 days.The Seattle Angina Questionnaire score and 6-minute walk test results will be evaluated at baseline and on days 30, 90, and 180.Echocardiography and carotid ultrasonography will be performed by the same physician at baseline and on days 90, and 180.Biological indicators: cardiac troponin I, creatine kinase isoenzyme-MB, total cholesterol, triglyceride, low-density lipoprotein cholesterol, apolipoprotein A1, apolipoprotein B, D-dimer, prothrombin time, activated partial thromboplastin time, thrombin time, fibrinogen, international standardized ratio, platelets, and immunoglobulin G will be assessed at baseline and on days 90 and 180.

#### 2.10.3. Safety evaluation.

Safety will be assessed based on the time and severity of adverse events, vital signs, blood, urine, and feces routine, laboratory measurements (liver and renal function, electrolytes), and electrocardiogram. Adverse events were defined as any adverse events or any deterioration of existing diseases that occurred from the first administration of TQAB or placebo to 7 days after the last administration. The spirit figure of enrollment, interventions, and assessments are shown in Figure 2.

**Figure 2. F2:**
[figure not shown]
Spirit figure of enrollment, interventions, and assessments. NXT, patients will be given 4 Nao-Xin-Tong capsules and one bag of placebo granules 3 times daily; BYHW, patients will be given one bag of Bu-Yang-Huan-Wu granules and 4 placebo capsules 3 times daily; YYTN, patients will be given one bag of Yang-Yin-Tong-Nao granules and 4 placebo capsules 3 times daily. Placebo, patients will be given one bag of placebo granules and 4 placebo capsules 3 times daily. NXT = Nao-Xin-Tong, SAQ = the Seattle angina questionnaire, YYTN = Yang-Yin-Tong-Nao.

### 2.11. Biological samples preservation

Biological samples will be collected and preserved in each center.

### 2.12. Sample size

The sample size estimation was based on a superior efficiency comparison between the 2 groups of rates. The following formula was used for estimation:

$$\begin{array}{l} n_{T}+n_{C}=(\frac{n_{T}\pi_{T}+n_{C}\pi_{C}}{n_{T}+n_{C}})(1-\frac{n_{T}\pi_{T}+n_{C}\pi_{C}}{n_{T}+n_{C}}){\left[\frac{\mu_{1-\alpha }+\mu_{1-\beta }}{\pi_{T}-\pi_{C}}\right]}^{2} \end{array}$$

$n_{T}$ and $n_{C}$ are the sample sizes for the treatment and control, respectively; α is the test level; β is the type-II error; 1-β is the power; and μ is the standard normal deviation threshold (μ1-α and μ1-β represent the corresponding one-sided bounds of 1-α and 1-β, respectively).

Assuming that the sample size ratio between the treatment and control groups is *r*, the above sample size formula is reduced to

$$\begin{array}{l} n_{T}=(\frac{\pi_{T}+\pi_{C}/r\;}{1+1/r\;})(1-\frac{\pi_{T}+\pi_{C}/r\;}{1/r\;}){\left[\frac{\mu_{1-\alpha }+\mu_{1-\beta }}{\pi_{T}-\pi_{C}}\right]}^{2} \end{array}$$

If π_T_ and π_C_ are the endpoints of observation of the efficacy of secondary prevention of myocardial infarction in the NXT and control groups, the incidence of endpoints was 5.6% and 15.4%, respectively. The Bonferroni adjustment was used to adjust α, α = 0.05/6 (unilateral), and β = 0.2. The NXT group consisted of 261 patients.

If π_T_ and π_C_ are the total response rates of myocardial infarction in the BYHW and control groups, respectively, the total effective rates were 92.30% and 76.92%, respectively. The BYHW group consisted of 146 patients.

If π_T_ and π_C_ are the total response rates of myocardial infarction in the YYTN and control groups, respectively, the total effective rates were 93.88% and 78.43%, respectively. The YYTN group consisted of 133 patients.

According to the Drug Registration Administration Measures and considering factors such as falling off, 673 patients are required.

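### The total of 673, the three calculated arm sizes, the printed formula and the 2:1:1:1 allocation do not agree, and no drop-out allowance is visible on top of the stated arms

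*Protocol article*

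**What the plan says.** Section 2.12 (Sample size) prints a two-proportion formula for the total and a reduced form for the treatment arm with allocation ratio r. It gives no value for r. The error rates are set once: "The Bonferroni adjustment was used to adjust α, α = 0.05/6 (unilateral), and β = 0.2".

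Three comparisons with control follow:

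- NXT: "the incidence of endpoints was 5.6% and 15.4%, respectively", leading to "The NXT group consisted of 261 patients".
- BYHW: "the total effective rates were 92.30% and 76.92%, respectively", leading to "The BYHW group consisted of 146 patients".
- YYTN: response rates of 93.88% and 78.43%, leading to "The YYTN group consisted of 133 patients".

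The section ends with "According to the Drug Registration Administration Measures and considering factors such as falling off, 673 patients are required". It gives neither a drop-out rate nor a size for the control arm.

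Section 2.7 (Randomization and grouping) has the same 673 patients "randomized into the NXT, BYHW, YYTN, and placebo groups in a 2:1:1:1 ratio".

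**The concern.** The three arm sizes are presented as results of the formula, and the total as what is needed after losses are considered. A reader would expect the total to exceed the sum of the arms by an identifiable margin, and the arms to follow from the allocation ratio. Neither is the case. The reduced formula as printed also cannot produce the sizes that follow it.

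At stake is whether the stated 80% power holds for the NXT comparison. NXT is the largest arm, and its power is limited by a placebo arm half its size. Follow-up runs to 180 days, so some loss is to be expected.

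**Working it through.** **Inputs.** From section 2.12: one-sided α = 0.05/6, β = 0.2, the three pairs of rates, arms 261/146/133, total 673. From section 2.7: ratio 2:1:1:1. Normal quantiles: 2.394 for one-sided 0.05/6, 2.638 for two-sided 0.05/6, 0.842 for 80% power. Not given, so varied here: r (1 or 2) and loss (0 to 20%, equal across arms).

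**1. The total.** 261 + 146 + 133 = 540, and 673 − 540 = 133. So 673 = 261 + 146 + 133 + 133 if control equals the YYTN arm. That control size is inferred.

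**2. The arm sizes.** The pooled-variance formula is n_T = (1+r)·p̄(1−p̄)·[(μ1-α+μ1-β)/(π_T−π_C)]², with p̄ = (π_T+π_C/r)/(1+1/r). For NXT the squared bracket is [(2.394+0.842)/0.098]² ≈ 1090. At r = 1, 2 × 0.105 × 0.895 × 1090 ≈ 204.9. At r = 2, 3 × 0.0887 × 0.9113 × 1090 ≈ 264.3. For all three comparisons:

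| Reading | NXT | BYHW | YYTN |
|---|---|---|---|
| Stated in section 2.12 | 261 | 146 | 133 |
| One-sided 0.05/6, 80% power, r = 1 | 204.9 | 115.3 | 104.6 |
| One-sided 0.05/6, 80% power, r = 2 | 264.3 | 148.5 | 131.6 |
| Two-sided 0.05/6, 80% power, r = 1 | 237.0 | 133.3 | 121.0 |
| Previous row, rounded, × 1.10 | 260.7 | 146.3 | 133.1 |
| One-sided 0.05/6, 90% power, r = 1, unpooled variance under the alternative | 262.0 | 146.4 | 132.6 |

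The fifth row rounds to exactly 261/146/133, but it is two-sided and 1:1. The third row uses the stated error rates and comes within 3% with no allowance. It applies 2:1 to BYHW and YYTN, which section 2.7 allocates 1:1 against placebo. The last row needs β = 0.1. No row satisfies both the stated error rates and the stated allocation.

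**3. The printed reduced formula.** Its second factor divides by 1/r where 1+1/r is needed, and the multiplier (1+r) is absent. At r = 2, NXT gives 0.0887 × [1 − 0.133/0.5] × 1090 = 0.0887 × 0.734 × 1090 ≈ 71. For BYHW the second factor is 1 − 1.3076/0.5 = −1.615, and the result is −623. YYTN gives −647. At r = 1 the three results are 90, −259 and −273.

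**4. The split.** 673/5 = 134.6, so 2:1:1:1 gives 269.2/134.6/134.6/134.6, about 269/135/135/135. Against the stated sizes NXT is 8 over, YYTN 2 over and BYHW 11 short (11/146 ≈ 8%).

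**5. Power as randomised.** Let s0 be the standard error under the pooled rate and s1 the one under the two separate rates. For 269 versus 135 at 5.6% and 15.4%, s0 = 0.02999 and s1 = 0.03408.

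- Unpooled alternative: (0.098 − 2.394 × 0.02999)/0.03408 = 0.77, power 78%.
- Pooled throughout: 0.098/0.02999 − 2.394 = 0.87, power 81%.

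| Assumed loss | NXT, unpooled alternative | NXT, pooled |
|---|---|---|
| 0% | 78% | 81% |
| 10% | 73% | 76% |
| 20% | 68% | 70% |

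Under the pooled formula NXT needs 264.3, so 80% is lost at 1 − 264.3/269 ≈ 2% attrition.

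For the other two arms at 135 versus 135 (unpooled alternative), BYHW has about 87% with no loss and 83% at 10%, and YYTN about 91% and 87%. At 20% loss (108 versus 108) BYHW falls to (0.1538 − 2.394 × 0.04911)/0.04798 = 0.755, about 78%.

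**The case against.** The strongest objection is that the identity in step 1 shows only that nothing was added after the arm sizes were fixed. A reader might infer that no drop-out allowance exists and that the closing sentence of section 2.12 is false. The document does not support that. A conventional 10% on a 1:1, two-sided 0.05/6 calculation reproduces all three arms exactly, so the allowance may already be inside them. The two-tailed threshold in section 2.13 makes a slip over sidedness plausible. This part of the objection stands.

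It does not rescue the plan. That calculation contradicts the one-sided alpha in section 2.12, and it needs about 237 evaluable controls for NXT where the allocation supplies about 135. At two-sided 0.05/6, NXT power with 269 versus 135 is about 71% with no loss and 66% at 10%, lower than under the stated alpha.

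Three further points stand in part:

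- The formula errors look typographical, and some could come from how the text was read. The published sizes cannot have come from a formula that returns negative values, so the misprint altered no patient number.
- A reader might infer that the 11-patient shortfall leaves BYHW below 80%. At the stated alpha it does not at 10% loss, and NXT and YYTN receive slightly more than stated.
- The NXT figure depends on the variance formula. Under the pooled one, 80% is just met with complete follow-up.

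**Conclusion.** The point holds as an inconsistency among figures the trial relies on. The total contains no visible allowance beyond the stated arms, the arms do not follow from 2:1:1:1, and the printed reduced formula cannot yield them. Whether an allowance was made inside the arms cannot be settled from the article.

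In consequence, the stated 80% for NXT is not kept once patients are lost. Power is about 73% at 10% loss, or 76% under the pooled formula. At 10% loss BYHW (about 83%) and YYTN (about 87%) remain above 80%.

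These figures assume the article's own event and response rates, one-sided 0.05/6, arms of 269 and 135 each, and equal loss across arms. The loss rates are assumptions because the article gives none. The control of 133 is inferred and does not enter the power figures.

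**What to change.** Revise section 2.12 as follows:

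- Print n_T = (1+r)·p̄(1−p̄)·[(μ1-α+μ1-β)/(π_T−π_C)]², with p̄ = (π_T+π_C/r)/(1+1/r), and bring the formula for the total into line with it.
- State r and the sidedness actually used for each comparison.
- List the four arms as randomised, about 269/135/135/135, including the control.
- State the drop-out rate and where it was applied. Only if none was applied, say that no allowance is included.
- Restate NXT power at 0%, 10% and 20% loss using one named formula, so that the formula and the power values match.

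The cost is the correction of one section and a less favourable stated power for NXT. No new patients are needed. A 2:1:1:1 total meeting every stated arm would be 292 + 146 + 146 + 146 = 730, but BYHW does not need its 146 to reach 80% at the stated error rates with 10% loss.

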### 2.13. Statistical analysis

Relevant logic verification will be conducted to determine the causes of participants’ falling off and missing data.

Statistical analysis will be performed using SPSS 15.0 (PN:32119001, SN:5045602) by a third party that has no access to the blinding codes. Continuous data will be expressed as mean ± standard deviation. Categorical variables will be expressed as frequencies (%). Continuous variables between the groups will be compared using the *t* test for normally distributed values. A completely randomized design and one-way analysis of variance will be used to compare normally distributed continuous variables with homogeneity of variance between groups, a completely randomized design and one-way analysis of variance will be used. The SNK-q test will be used for pairwise comparisons between groups. The rank-sum test will be used to compare non-normally distributed continuous variables between groups. Comparisons between groups will be performed using the chi-square test (or Fisher’s exact test when the expected frequency is <5). Post hoc analysis was performed using LOGISTIC and COX regression analyses. All calculations will be performed using SPSS 15.0. The threshold for significance will be set to *P* < .05 (2-tailed).

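### Continuous secondary outcomes are tested without a baseline or centre term, and SNK-q can let the pairwise family-wise error rise to about 9.75% in one pattern of the four arm means.

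*Protocol article*

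**What the plan says.** Section 2.13 (Statistical analysis) sets the tests by type of data. For normally distributed variables it says "Continuous variables between the groups will be compared using the *t* test for normally distributed values". It then names one-way ANOVA where variances are homogeneous, and adds "The SNK-q test will be used for pairwise comparisons between groups". Non-normal variables go to the rank-sum test. The significance threshold "will be set to *P* < .05 (2-tailed"). The only regressions named are logistic and Cox, both as post hoc analyses, and neither is a model for a continuous outcome.

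Section 2.10.2 (Secondary outcomes) gives the measurement times. The Seattle Angina Questionnaire score and "6-minute walk test results will be evaluated at baseline and on days 30, 90, and 180". Echocardiography, carotid ultrasound and the laboratory indicators are measured at baseline and on days 90 and 180. Each outcome therefore has a baseline and either three or two later visits.

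Section 2.7 stratifies randomisation by centre, with patients "randomized into the NXT, BYHW, YYTN, and placebo groups in a 2:1:1:1 ratio". Section 1 sets out to judge whether the three preparations work alike, so drug-versus-drug contrasts are an aim alongside drug versus placebo.

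**The concern.** There are two separate weaknesses in how the continuous secondary outcomes are analysed.

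- **Precision.** The tests named have no baseline covariate, no centre term and no link between visits. The trial pays to measure each outcome at baseline and then does not use that measurement to reduce noise in the comparison. The Discussion names quality of life, with heart failure, as what the trial observes, so the angina questionnaire matters to the trial's message.
- **Pairwise error.** SNK-q is a step-down range test. A pair of arms that are adjacent once the means are ordered is tested at the full 5% as soon as the wider ranges containing it are significant. With three arms at most one true null is exposed in this way. With four arms two can be, and the chance of at least one false claim then exceeds 5%. The sample size section shows that multiplicity was considered ("The Bonferroni adjustment was used to adjust α, α = 0.05/6 (unilateral), and β = 0.2"), but section 2.13 does not carry that adjustment through.

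**Working it through.** **Inputs from the article.** Four arms at 2:1:1:1 (section 2.7); 673 patients (section 2.12); two-sided 0.05 (section 2.13); visits as in section 2.10.2. By arithmetic 673/5 = 134.6, so the arms are taken as 269, 135, 135 and 134, with 673 − 4 = 669 error degrees of freedom. Four arms give 4 × 3/2 = 6 pairs.

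**No planned figure to reproduce.** The article states no standard deviation, effect size, correlation, power or family-wise rate for the continuous outcomes. Its sample sizes rest on event and response rates.

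**Step 1: precision.** Let σ² be the variance of the outcome, taken as equal at baseline and follow-up, and ρ their correlation. Per patient:

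- follow-up value alone: σ²
- change from baseline: 2σ²(1 − ρ)
- ANCOVA on baseline: σ²(1 − ρ²)

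The ratio of ANCOVA to follow-up value is 1 − ρ². The ratio to change is (1 − ρ²)/[2(1 − ρ)] = (1 + ρ)/2. The values of ρ are assumptions.

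| Assumed ρ | ANCOVA / follow-up value | ANCOVA / change |
|---|---|---|
| 0.3 | 0.91 | 0.65 |
| 0.5 | 0.75 | 0.75 |
| 0.7 | 0.51 | 0.85 |

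At ρ = 0.5, leaving baseline out costs as much as needing 1/0.75 = 1.33 times the patients. A follow-up-value comparison that happened to have 80% power would have about 84%, 90% or 98% power with adjustment at the three values of ρ.

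**Step 2: SNK-q in theory.** Suppose two arms share one mean, the other two share another, and the two means are well apart. The wider ranges are then almost always significant, so each equal pair is tested at 5%. The two tests are nearly independent, and the family-wise error is 1 − (1 − 0.05)² = 1 − 0.9025 = 9.75%. Arm sizes do not enter this expression.

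**Step 3: SNK-q at the trial's arm sizes.** The procedure was simulated with 5% studentised-range critical values of 2.777, 3.322 and 3.642 for spans of 2, 3 and 4 means. Both common forms for unequal groups were used: pairwise standard errors and the harmonic-mean n. Rows marked * use 40,000 runs; the others use 200,000.

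| True means | Family-wise error |
|---|---|
| All four equal | 4.8% (pairwise), 5.3% (harmonic) |
| Three equal drugs, 0.2 to 1.5 SD from placebo* | 3.8% to 4.8% |
| Two equal pairs, 0.2 SD apart* | 6.6% to 6.9% |
| Two equal pairs, 0.3 SD apart | 9.0% to 9.2% |
| Two equal pairs, 0.5 SD or more apart | 9.6% to 9.9% |

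With the harmonic-mean n, the 2:1:1:1 ratio moves the level of single pairs, to about 3.4% for NXT against a small arm and 6.7% for two small arms. The combined rate hardly changes: 1 − 0.966 × 0.933 = 9.9%.

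**Step 4: Tukey-Kramer.** It uses the span-4 value for every pair: 3.642/√2 = 2.58 on the t scale, about 1.0% per pair. In the two-pair case the family-wise error is 1 − 0.99² ≈ 2.0%, and it is at most about 5% overall.

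**The case against.** The strongest reply is that section 2.13 is a generic list of tests in a condensed article. Covariates, the choice between values and changes, and repeated-measures models usually belong to a fuller plan, which is not shown. Unadjusted comparison in a randomised trial is also unbiased, so adjustment is a gain in efficiency and not the repair of an invalid test. The second part stands. The first does not dispose of the point, because the article names the tests outright, and a fuller plan would have to replace them, not merely add to them.

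A reader might infer several stronger things that the article does not support:

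- **That SNK-q runs at 10% here in general.** It does not. It stays near 5% if nothing differs, and also if the three drugs are equally effective and differ from placebo, which is the pattern the trial hopes to show.
- **That the 2:1:1:1 allocation causes the excess.** The 9.75% arises equally with equal arms.
- **That a promised 5% family-wise level is broken.** Section 2.13 states a significance threshold and makes no family-wise claim for these contrasts.
- **That baseline is certainly ignored.** Changes from baseline may be what is compared. At ρ = 0.7 the variance reduction is then 15%, not 49%.
- **That six unadjusted t tests are planned,** with about 20% family-wise error under the global null. SNK-q is the method named for pairs.
- **That cardiac function is a main aim.** The Discussion's stated aim is heart failure incidence and quality of life; cardiac function appears there as background on the treatment.

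**Conclusion.** The point holds in a limited form. The named analyses of the continuous secondary outcomes give away precision for any non-zero baseline correlation, whether follow-up values or changes are compared. The size of the loss rests on an assumed ρ and on equal variances at baseline and follow-up. SNK-q with four arms does not control family-wise error in every configuration. The worst case is about 9.75% per outcome and visit, and needs two equal pairs of arms about 0.5 SD or more apart. That pattern cannot be ruled out in a trial that asks whether its drugs differ from one another. The primary outcome is categorical, goes to the chi-square or Fisher's exact test, and is not touched. This is a worthwhile correction to secondary analyses, not a threat to the trial's main conclusion.

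**What to change.** In section 2.13, analyse each continuous secondary outcome by ANCOVA with arm, baseline value and centre at each visit. Alternatively, use one repeated-measures mixed model with baseline × visit, arm × visit and centre. Outcomes now sent to the rank-sum test lose the baseline in the same way; whether to model them after transformation or keep a rank method can be left to the analysis plan.

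Replace SNK-q with Tukey-Kramer for all six pairs, because drug-versus-drug comparison is an aim of the trial. Dunnett would suit only a family limited to drug versus placebo.

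The cost is wording and a little more analysis work, with no new data, visits or patients. The pairwise test becomes more conservative for arms adjacent in order, where the bar moves from 2.777/√2 = 1.96 to 2.58 on the t scale. The change should be made before unblinding.
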